#### Covariates

The covariates are as follows.

Familiarity with science will be measured by 1 item asking, “How often do you read science papers or science in the news?” (1=never to 5=always) [32]; this item was suggested in Song et al [32] as being potentially important to considerLevel of religious commitment (0=low to 10=high), as used in our previous studies [19,20,41]Political orientation (0=liberal to 10=conservative), as used in our previous studies [19,20,41]Political party (Republican, Democrat, or other), given recent research suggesting divergence between political orientation and party orientation pertaining to face masks [42]Race, ethnicity, gender, age (“About how old are you (*in years*)?”), and education level (“What is the highest grade or level of school you have completed, or the highest degree you have received?”) [43]

#### Statistical Analyses

Descriptive statistics of demographics and outcomes will be calculated. We will explore distributions of trust in science (Hypothesis 1) and each of the single-item measures (Hypotheses 2-5).

Data will be analyzed using analysis of covariance (ANCOVA), with the assignment of the study arm (intervention vs control) used as the independent variable and the specified outcomes (depending on the hypothesis) set as the dependent variable. All specified covariates will be included in each model, and assumptions for the analyses will be evaluated (eg, the normality of residuals and linear relationships between covariates and the dependent variable). If assumptions are not met, the research team will explore different transformations or nonparametric models as recommended by statistical experts.

Missingness is not anticipated owing to the study design, but if it occurs at a meaningful level (>5%), we will perform sensitivity analysis using Multiple Imputation by Chained Equations to explore how missingness affects the results, and in the case that the results differ, we will report Multiple Imputation by Chained Equations as the primary analysis.

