### Design

#### Trial Design

We will conduct a randomized controlled trial consisting of 2 parallel groups and a 1:1 allocation ratio. Our planned study workflow is provided in Figure 1. Allocation will be automated by the Randomizer feature in the QualtricsXM platform [33] and thus, by definition, will be concealed from researchers until after each case has been assigned. However, we note that based on our prior experience, the use of data quality checks and the 2-step survey completion procedures in the Prolific platform can result in unbalanced allocation for a very small portion of the sample as recruitment approaches the planned limit (eg, if the number of usable surveys exceeds the number of surveys solicited, the excess surveys may not be allocated 1:1 but will still be included following sensitivity analysis) [20].

This study will be, in principle, a double-blind study; participants will be unaware that they are being randomized to a condition, and allocation will be done exclusively by software. However, analysts will not be blinded to the meaning of the group assignment variable.

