### Sampling Plan

#### Sample Size Determination and Power Analysis

As previously described, we will recruit 1500 individuals from the Prolific platform, with equal allocation to study arms. This sample size is currently the largest number of people for which the Prolific platform can assure national representativeness. We made the decision to recruit a large number of participants because we were unable to locate any baseline studies with which to estimate effect size, so we wanted to be conservative. In addition, although the issue of face masks continues to be a point of public contention, the prevalence of public health mandates related to face masks is lower than those in 2020-2021, which we suspect may serve to suppress the effect size relative to what it would be in the midst of more active social discord focused on that topic. With 80% power (2-tailed test), this sample will allow us to detect small effects at α=.05 (Cohen *d*=0.14) and at corrected α=.01 (Cohen *d*=0.18) for differences of trust in science between treatment and control. In keeping with modern inferential statistical recommendations, we will report all *P* values precisely rather than by threshold [40] and provide a balanced interpretation, especially where .01<*P*<.05.

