### Analysis Plan

#### Primary Outcomes

The primary outcomes are as follows.

Hypothesis 1Overall trust in science and scientists will be measured by the 21-item scale developed and validated by Nadelson et al [18]. An example item from the scale measures agreement with the statement, “When scientists change their mind about a scientific idea it diminishes my trust in their work.” This scale has demonstrated excellent internal reliability in our previous studies with crowdsourced samples (α>.900) [19-22,41].Hypotheses 2 through 5Single-item measures of credibility and trust that are specific to the hypothetical social media post and the scientist who conducted the study, from Song et al [32]“How credible is the scientist who conducted the study described in the post?” (1=not credible at all to 7=extremely credible); note that this language is slightly different than the original item to avoid ambiguity arising from the potential that a scientist authored the social media post“How credible is this research?” (1=not credible at all to 7=extremely credible)“I would trust scientific information if I knew it came from this author.” (1=strongly disagree to 7=strongly agree)“I trust this scientific information.” (1=strongly disagree to 7=strongly agree)

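### Residual normality is the wrong trigger for leaving ANCOVA, and the open fallback leaves unclear which analysis is primary for the five outcomes

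*Protocol article*

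**What the plan says.** The Statistical Analyses section of the protocol article fixes the model: "Data will be analyzed using analysis of covariance (ANCOVA), with the assignment of the study arm (intervention vs control) used as the independent variable". All listed covariates enter each model. Table 1 repeats ANCOVA with the nine covariates for Hypotheses 1-5 and shows no fallback.

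The same section then says "assumptions for the analyses will be evaluated (eg, the normality of residuals and linear relationships between covariates and the dependent variable", and continues: "If assumptions are not met, the research team will explore different transformations or nonparametric models as recommended by statistical experts". It gives no criterion for failure, no named transformation or model, and no statement of whether ANCOVA stays primary.

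Two other places bear on this. Under Primary Outcomes, Hypothesis 1 uses a 21-item scale. Hypotheses 2-5 each use one 7-point item: two credibility items scored "1=not credible at all to 7=extremely credible" and two agreement items, also scored 1 to 7. Under Trial Design, the article states that "analysts will not be blinded to the meaning of the group assignment variable".

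**The concern.** A variable with seven possible values cannot give exactly normal residuals, and a sample of 1500 gives a formal test ample power to show it. For four of the five primary outcomes the fallback is therefore a likely path and not a remote contingency. The trigger also has little bearing on whether the planned test is valid. With about 750 per arm, the adjusted mean difference is close to normally distributed whatever the shape of the residuals.

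Three things are at stake. First, a transformed or rank-based outcome answers a different question from the mean difference on which the detectable effects rest. Second, the 21-item scale may stay on its original scale while the single items move to another, so the five results would not be comparable. Third, the choice is open and would be made by people who can see the arm labels.

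**Working it through.** **Inputs from the article.** 1500 participants with 1:1 allocation, so 750 per arm; two-sided tests; 80% power; α of .05 and corrected .01; stated detectable effects d = 0.14 and 0.18; four outcomes scored 1 to 7.

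**Inputs assumed.** The article gives neither the distribution of the items nor the strength of the covariates. I took a latent normal variable cut into seven categories in three ways: symmetric, skewed (mean residual skewness -0.97) and strong ceiling (-1.75). Three covariates had coefficients .35, .2 and .1, which explain .35² + .2² + .1² = .1725, about 17%, of the latent variance. There was no arm effect.

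**Step 1: the plan's own figure.** Detectable d = (z for α/2 + z for power) × √(2/750).
- α = .05: (1.960 + 0.842) × 0.05164 = 0.145, stated as 0.14.
- α = .01: (2.576 + 0.842) × 0.05164 = 0.176, stated as 0.18.

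Both reproduce to within rounding. They are standardised mean differences on the original scale.

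**Step 2: would a normality test reject, and does it matter?** There were 3000 simulated trials per shape, with Shapiro-Wilk at .05 applied to the residuals in 1000 of them.

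| Item shape | Normality rejected | ANCOVA type I error, nominal .05 | nominal .01 |
|---|---|---|---|
| Symmetric | 84.5% | .052 | .011 |
| Skewed | 100% | .051 | .011 |
| Strong ceiling | 100% | .045 | .011 |

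The simulation standard error at nominal .05 is √(.05 × .95/3000) = .004, so all three values are compatible with .05. A separate simulation of a skewed item, with stronger covariates (latent R² about .26), rejected normality in 300 of 300 data sets. ANCOVA type I error there was 5.0% with either classical or HC3 standard errors.

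**Step 3: what an open choice could do to type I error.**
- *Choice by P value.* Taking the smallest P of ANCOVA, ANCOVA on log(8 - y), ANCOVA on y² and Mann-Whitney gave 8.0-8.4% at nominal 5% and 1.8-1.9% at nominal 1%. With rank ANCOVA as a fifth candidate, the separate simulation gave 9.1% and 1.9%.
- *Choice by residual shape.* Taking whichever of the raw, reflected-log, squared or rank ANCOVA had the most nearly normal residuals (highest Shapiro-Wilk W) gave 5.3%, 5.1% and 5.0% at nominal 5%, and 1.0%, 1.1% and 1.0% at nominal 1%. Further runs of a shape-driven choice ranged from 4.4% to 5.5% at nominal 5%.

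**Step 4: the estimand.** On the log(8 - y) scale, the step between scores 6 and 7 is ln 2 - ln 1 = 0.693, while the step between 1 and 2 is ln 7 - ln 6 = 0.154. One point at the top then counts 0.693/0.154 = 4.5 times as much as one point at the bottom. That is no longer the mean difference in Step 1.

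**The case against.** Four stronger readings are tempting, and the article does not support them.

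- *The team will replace ANCOVA.* The sentence says only that alternatives will be explored. The missing-data paragraph that follows states outright when multiple imputation becomes primary; nothing like that is attached to this fallback. Whether it replaces or supplements is unclear.
- *Normality is the single gate, and any check must fail.* It is one of two examples, and no test is named. A formal test would probably reject, but a graphical check could pass.
- *The covariates would be dropped.* The article speaks of nonparametric models, shortly after requiring all covariates in each model. A rank ANCOVA would fit that wording; an unadjusted rank test is only one possible reading.
- *Type I error will be about 9%.* That needs selection by P value. The article describes a choice prompted by failed assumptions and guided by statistical experts, and Step 3 shows no inflation for a choice driven by residual shape.

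There are also partial safeguards: exact P values, balanced interpretation, and release of raw data and code. These make selection detectable afterwards, but they do not fix the choice beforehand.

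Finally, the exact diagnostic and the order of fallbacks could sit in a separate analysis plan. That is fair for missing detail. It does not answer the point that the stated rule lets a diagnostic with little bearing on validity unsettle a sound primary analysis.

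**Conclusion.** The concern holds in limited form. The planned ANCOVA is sound for all five outcomes at this sample size, and the rule for departing from it rests on the wrong property. For the four 7-point items a formal normality test would reject in about 85% to 100% of cases, while ANCOVA type I error stays near nominal. The likely costs are an altered estimand, results on different scales across Hypotheses 1-5, and doubt about which analysis is primary.

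Inflated type I error is a possibility and not an expected result: about 8-9% at nominal 5%, and just under 2% at nominal 1%, per outcome, as an upper bound under P-value selection. All simulated figures rest on the assumed item distributions and covariate strengths. The conclusion about ANCOVA rests mainly on the size of the arms and was the same for every shape tried. The plan should be changed, but the fault does not undermine the trial.

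**What to change.** Replace the fallback sentence with a fixed rule:

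- Covariate-adjusted ANCOVA with heteroscedasticity-robust (HC3) standard errors is the primary analysis for all five outcomes, whatever the residuals look like.
- Diagnostics are reported to describe the data and do not change the primary analysis.
- One proportional-odds model with the same nine covariates is the named sensitivity analysis for Hypotheses 2-5.

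The robust errors guard against unequal variances; the simulations show no need for them on grounds of residual shape alone. The proportional-odds model carries its own assumption, which is acceptable in a supporting role. Masking the arm labels until the analysis code is locked is a useful option but is not essential once the model is fixed.

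The cost is one replaced sentence, a few lines of code, a little extra reporting, and a negligible loss of efficiency if the variances are in fact equal.

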### Data and Code Availability

Raw data will be included as a digital supplement in each format needed to execute the included code (eg, .csv and .sav) alongside the full paper when published. All code needed to replicate the specific data cleaning and analysis steps in this paper will be included as a digital supplement alongside the full paper when published.

## Results

This protocol was prepared in full and submitted for review prior to any data collection or subject recruitment. The study will be conducted without using any external funding mechanisms. Results are expected to be published in late 2022 or early 2023.

## Discussion

### Expected Findings

This study is designed to determine whether the use of normative language in addition to cognitive language has an effect on a variety of measures related to general and specific trust in science and scientists as well as the credibility of the claims and their author(s). As indicated previously, we expect to see lower levels of general and localized trust in science and as well as reduced perceptions of credibility of both the post and the scientist(s) conducting the study among study participants who are exposed to both a cognitive and normative claim about a study than those exposed only to a cognitive claim.

### Next Steps

If 1 or more of our hypotheses are correct, then we hope to use these findings to initiate discussions about research dissemination and communication and the ways in which communication about research findings might more closely attend to and explicitly draw distinctions between cognitive and normative claims. This discussion may include conversations around changing the ways in which scientists communicate generally and addressing the complexity of separating normative and cognitive claims when communicating outside of the field (eg, with the media or policy makers).

We plan to disseminate the results of this study regardless of the findings through peer-reviewed publications as well as other avenues, as appropriate.

### Limitations

We anticipate that this study design may result in several limitations to its interpretation. First, we cannot control the conditions in which people participate; thus, although we will incorporate comprehension checks for the intervention, we cannot be assured that all participants will sufficiently engage with the intervention content. Second, since this is a web-based study through the Prolific platform, even though the results have a degree of national US generalizability, they still reflect the unique characteristics of those who have signed up for the Prolific platform as well as, by extension, those who actively use the internet. In a recent protocol for our COVID-19 intervention study, we outline why we believe these concerns are somewhat attenuated for this type of experiment [44]. Other limitations may be identified during the study itself or by reviewers at each stage of the project and will be noted after their identification.
